#### Identifying prognostic factors

Multivariate regression analysis will also be applied to investigate to what extent child characteristics and FRO stiffness represent determinants for success of FRO treatment, defined as decreased walking energy cost (model 1), improvement in daily activity (model 2) and positive GAS scores (model 3). Initially, a univariate regression analysis (ANOVA) will be performed to determine which factors are significantly associated with FRO treatment outcomes (p≤0.1). Significant factors (p≤.05) will then be included in a multivariate regression model. Model analysis will include factors such as level of physical fitness, baseline disease characteristics, gait pattern, level of functional mobility, environmental factors and FRO characteristics.

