#### Sample size

The sample size will be based on a power analysis of the expected changes (i.e. T0 versus T2) in the primary outcome, walking energy cost [J^-1^⋅kg^-1^⋅m^1^. According to literature, walking energy cost in children with CP may be 30-50% higher than in healthy children
[10-12]. SCP children with GMFCS levels I, II and III show a mean net EC of 5.02 (±1.70) J^-1^⋅kg^-1^⋅m^1^[26]. A reduction of 25% in this value (≈1.26 J^-1^⋅kg^-1^⋅m^1^) is considered to be a clinically significant change
[25,26]. Assuming a power of 80% and a significance level of 0.05, detecting a clinically significant change will require a sample size of 29 children
[44]. Allowing for a dropout of approximately 10%, a sample size of 32 will be sufficient.

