***Other outcomes***				
	GAS	x		x
	FRO properties	x	x	x
	Motivation diary	x	x	x
	@ monitor		x	x
	Satisfaction	x	x	x

*T1_k_ will be repeated for each FRO-configuration: rigid, stiff and flexible.

** The physical examination includes passive Range of Motion, selective motor control and gross motor function tests.

***SAM and CAPE data will be assessed in the week prior to the ticked measurement moment.

BSS=’Bronnen van Steun en Spanning’; CAPE=Children’s Assessment of Participation and Enjoyment; ECWT=Energy Cost of Walking Test; FAQ=Functional Assessment Questionnaire; FMS=Functional Mobility Scale; FRO=Floor Reaction Orthosis; GAS=Goal Attainment Scaling; GMFCS=Gross Motor Function Classification System; SAM=StepWatch3^TM^ Activity Monitor.

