##### Physical fitness

Physical fitness will be measured by means of an aerobic and anaerobic exercise test on a bicycle ergometer. The aerobic test will be performed according to the protocol described by Balemans et al.
[53] and aerobic fitness will be defined as oxygen uptake over the 30 seconds with the highest sustained load (VO2_peak_) [ml^-1^⋅kg^-1^⋅min^-^1]. Anaerobic power will be determined using the 20 seconds Wingate Anaerobic cycling Test (20s-WAnT), a sprint test against a constant breaking torque
[54]. Anaerobic fitness will be defined by the mean anaerobic power over 20 seconds (P20_mean_) [W⋅kg^-1^ and by the highest power output within the 20 seconds, the peak anaerobic power (P20_peak_) [W⋅kg^-1^. Measurement procedures, equipment and protocols for both tests will be as described by Balemans et al.
[53].

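### Predictors of FRO success are picked by univariate p-value screening of an open list (about 13–14 candidates) in about 29 children, so the resulting p-values and R² are not valid evidence of prediction

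*Protocol article*

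**What the plan says.** The procedure is fixed in the protocol article under Statistical analysis, Identifying prognostic factors.

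- **Screen:** "Initially, a univariate regression analysis (ANOVA) will be performed to determine which factors are significantly associated with FRO treatment outcomes (p≤0.1".
- **Next step:** "Significant factors (p≤.05) will then be included in a multivariate regression model".
- **Outcomes:** success is "defined as decreased walking energy cost (model 1), improvement in daily activity (model 2) and positive GAS scores (model 3".
- **Candidates:** "Model analysis will include factors such as level of physical fitness, baseline disease characteristics, gait pattern, level of functional mobility, environmental factors and FRO characteristics". The list is open and no number is given.

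That section mentions no adjustment for the number of factors tested, no shrinkage, no validation and no exploratory label. Background makes the search for predictors of success part of the second of the two main goals. Sample size gives 29 children, or 32 with dropout, and is derived only from the expected change in walking energy cost.

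**The concern.** A factor that enters a model because its p-value was small in the same data will tend to look significant there. The final p-values and R² do not account for the candidates that were tried and discarded. With nearly half as many candidates as children, and three outcomes, the procedure can yield a predictor with a respectable R² when nothing predicts anything.

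The two thresholds add to this. The screen is set at 0.1, but the next sentence says that factors significant at .05 are included. That could be a second, stricter entry rule, or a significance level for the final model. Evaluation of FRO efficacy uses similar two-threshold wording for the working-mechanism models.

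At stake is the prediction half of the second main goal. Background motivates it by the wish to identify children who could benefit from an FRO. The primary paired comparison is not affected.

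**Working it through.** **1. Sample size (Sample size section).** SD 1.70, difference 1.26, power 80%, two-sided 0.05 (sidedness assumed): 2 × (1.960 + 0.842)² × 1.70² / 1.26² = 28.6, so 29, as stated. Dropout: 29 × 1.1 = 31.9, so 32. I use n = 29.

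**2. Number of candidates.** Counting one variable per listed measure:
- Physical fitness: 3 (VO2peak, mean and peak anaerobic power).
- Physical examination: 3, since "The physical examination includes passive Range of Motion, selective motor control and gross motor function tests".
- Other effect-modifier rows of Table 2: 6 (gait pattern, intake questionnaire, BSS, FMS, FAQ, GMFCS).
- FRO stiffness: 1.

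The sum is 13. The Effect modifiers section also names demographic variables, and at least one more makes 14. This is my count.

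**3. Chance of passing the screen, independent noise candidates.** P(at least one) = 1 − (1 − α)^k.
- k = 14, α = 0.1: 1 − 0.9^14 = 77%; expected false selections 14 × 0.1 = 1.4.
- k = 14, α = 0.05: 1 − 0.95^14 = 51%; expected 14 × 0.05 = 0.7.
- k = 13: 75% and 49%.

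**4. Full procedure by simulation.** Outcome and 14 candidates are pure noise, n = 29. Each candidate is screened singly, survivors are fitted jointly by least squares, and terms at p≤.05 are counted. There were 3000 runs for one outcome and 1500 for three. Both readings of the threshold were tried. Rates are per outcome; small ranges show the spread between repeated runs.

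| Candidate correlation | Any passes 0.1 screen | Final term p≤.05, entry at 0.1 | Final term p≤.05, entry at 0.05 |
|---|---|---|---|
| 0 | 77% | 43–44% | 49% |
| 0.3 | 68% | 27% | 32–36% |
| 0.5 | 58% | 13–14% | 20–22% |

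**5. Three outcomes, assumed independent, entry at 0.1.** From the per-outcome rates: 1 − (1 − 0.426)³ = 81% at correlation 0 and 1 − (1 − 0.136)³ = 36% at correlation 0.5. Direct simulation gives 80% and 36%; overall about 35–80%.

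**6. Apparent R² when the truth is 0, entry at 0.1.** Among analyses that select something, the mean is 0.235 (correlation 0) to 0.197 (0.5). Counting R² as 0 when nothing is selected: 0.235 × 0.768 = 0.18 and 0.197 × 0.583 = 0.11. Selection forces the high values: at n = 29 a candidate passes 0.1 only if |r| is at least 0.311, which is an R² of 0.311² = 0.10.

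**7. Sensitivity.** With n = 32 and correlation 0 the results are 77% (screen) and 43% (final). With only 6 candidates, one per named class, and entry at 0.1, a final term reaches p≤.05 in 23%, 18.5% or 11% per outcome at correlation 0, 0.3 or 0.5.

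**The case against.** - **For a single outcome, a false predictor is not the likely result.** This stands. A reader might take the 58–77% as the rate of false predictors, but passing the 0.1 screen is not yet a claim. In the final model the rate is below one half in every scenario. It exceeds one half only when pooled over the three outcomes with weakly correlated candidates. Some correlation is plausible: mean and peak anaerobic power come from the same sprint test, and FMS, FAQ, GMFCS and gross motor function all describe mobility.
- **The candidate count is not in the document.** This stands, and a final list may properly be left to a fuller plan. But the screening method is stated in the article, and 13 instead of 14 hardly changes the result.
- **The aim is worded modestly.** The Abstract speaks of potential predictors, and no rule for selecting children is promised. This tempers the consequence. It does not make p-values computed after selection valid, and Background still lists prediction as a main goal.
- **Success as any decrease, yes or no.** A reader might infer this and set it against the 25% reduction called clinically significant under Sample size. The documents do not support it: no responder threshold or logistic model is stated, and the parallel analysis under Evaluation of FRO efficacy is linear regression on changes. Decreased energy cost reads naturally as the direction of benefit.
- **FMS and FAQ from later visits as predictors.** A reader might infer this from Table 2, which has both measured at all visits. The article nowhere says that later values would be used.

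**Conclusion.** The concern holds for the selection procedure. Followed as written, and under either reading of the thresholds, it gives p-values and R² that are not valid as evidence of predictors. With 14 noise candidates and 29 children, a false final-model term appears in about 13–44% of analyses per outcome with entry at 0.1, and about 20–49% with entry at 0.05. Over three outcomes with entry at 0.1 it is about 35–80%. Mean apparent R² is about 0.20–0.24 where something is selected and about 0.11–0.18 over all analyses.

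These sizes rest on assumptions that the documents do not supply: one variable per measure, candidate correlations of 0 to 0.5, independent outcomes, and continuous outcomes fitted by least squares. Positively correlated outcomes would lower the three-outcome figure; several scores per instrument would raise the number of candidates.

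**What to change.** - Drop the univariate screen, and with it the conflict between 0.1 and .05.
- For each outcome, name a small number of baseline candidates in advance, for example two or three, and enter them together whatever their univariate p-values.
- If the full list is to be explored, use penalised regression with a bootstrap optimism-corrected R² and label the results hypothesis-generating. Penalised selection is itself unstable at n = 29, so the label matters.

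With two or three independent candidates tested at 0.05, the chance of any false result per outcome is 1 − 0.95² = 10% or 1 − 0.95³ = 14%. If candidates correlate at 0.5 and entry is at 0.1, the screen already gives about 13–14%, so the gain in that rate would be small. The gain that remains is that each p-value keeps its nominal level and R² is free of selection.

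The change needs revised wording and slightly more analysis work, with no new data, visits or children. The downside is that fewer factors can be claimed as predictors. Two or three is a judgement, not a figure from the documents.

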## Discussion

This study will evaluate the effects of varying degrees of FRO ankle stiffness on different aspects of gait. Based on earlier studies, an optimal match is expected between specific patient characteristics and FRO stiffness. Assuming that there is an optimal FRO stiffness for each subject, this study might lead directly to an optimised FRO treatment for these patients. In addition, the study will evaluate FRO efficacy, using outcome measures that are relevant in the patient’s daily life (i.e. walking energy cost and daily activity), thereby emphasising clinical relevance.

Because the stiffness of an FRO should be based on the specific gait deviations of the child, the inclusion criteria of this study will be specifically defined. This will result in a relatively homogeneous study population, enabling a fair comparison of subjects. On the other hand, these strict criteria may make it difficult to generalise results to the wider treatment and prescription of FROs, also because the design of the investigational FRO design differs from conventional FROs. Nonetheless, it is expected that the results of the study will allow an optimal FRO treatment to be defined in this specific patient group.

This study will be the first to investigate broadly the efficacy of an individually optimised FRO, including evaluation of effects on multiple ICF levels. This will result in a unique data set with which to assess mutual relations between outcome measures. We anticipate that this analysis will aid in identifying both the underlying working mechanisms of FRO and the factors important to treatment success. In conclusion, the data generated by this study may provide not only novel insights, but may also contribute to improved FRO treatment in SCP in the (near) term.

## Abbreviations

AFO: Ankle-Foot Orthosis; FRO: Floor Reaction Orthosis; GMFCS: Gross Motor Function Classification System; ICF: International Classification of Functioning, Disability and Health; ROM: Range of Motion; SCP: Spastic Cerebral Palsy.
